### Outcomes measures and data collection

Outcomes and assessments are guided by the conceptual framework (Fig. 1) and represent either our outcomes or potential determinants/moderators of outcomes.

#### Patient

The primary outcome, Reach, is defined as the proportion of tobacco users who enroll in UTQL treatment. Patient enrollment in the UTQL (i.e., the numerator of Reach) will be assessed and obtained from the UTQL vendor on a continuous basis throughout the duration of the study. The total number of tobacco-using patients seen at participating clinics (i.e., the denominator of Reach) will be gathered from the EHR at participating clinics on a continuous basis. Use of tobacco/nicotine products (e.g., smokeless, cigars, e-cigarettes, vaporizers) and patient demographics (e.g., race/ethnicity, insurance status, primary language, age) will be collected via the EHR.

The other primary outcome, Impact, is defined as the product of Reach and Efficacy. Efficacy is defined as patient abstinence status at 12 months following the patients’ initial clinical encounter among patients who enrolled in the UTQL. Tobacco-using patients will be contacted to complete a self-report abstinence survey at 12 months following the initial clinical encounter. Patient self-reported abstinence status will be assessed using recommendations for cessation induction trials (i.e., 7- and 30-day point prevalence abstinence) [63]. A subset of patients (*n* = 300) self-reporting abstinence at 12 months will complete biochemical verification of abstinence (i.e., cotinine) using mailed saliva sample kits.

#### Clinic and organization

CHC system and clinic practice team implementation determinants and outcomes will be assessed via staff surveys, qualitative interviews, data from Uniform Data System (UDS) reporting (i.e., the standardized reporting system) [64], and the EHR. We will conduct in-depth interviews with clinic staff halfway through study completion that will be recorded and transcribed for analysis. We will conduct a thematic content analysis using iterative and deductive coding to better understand implementation in clinics and further inform dissemination efforts [65–68]. We will collect survey data on implementation determinants from staff from each clinic (e.g., medical assistants, nurses, doctors, clinic directors) at three time points (i.e., prior to AAC implementation, midway through study completion, at the conclusion of patient follow-up). Assessments will measure changes in implementation self-efficacy, outcome expectations, and behavioral capabilities (Fig. 1). We will assess selected constructs from key CFIR domains such as the inner setting, intervention characteristics, outer setting, characteristics of individuals, and process [55]. We will obtain data on clinic characteristics such as number of patients served each year, patient demographics, and health insurance status, from UDS. We will collect data regarding fidelity of the clinic practice team to administering AAC routinely from the EHR.

### Statistical analyses and power calculations

#### Analytic plan

The richness of the three-phase SMART design provides the opportunity to test multiple hypotheses [69, 70]. Our primary hypotheses address the capability of the specific interventions in each phase to extend Reach and Impact beyond the preceding phase: Is AAC- Out superior to AAC-In at 2 weeks? Is TM superior to CO at 6 months among those who fail to use the Quitline after the ACC interventions? Is TM + MAPS superior to TM-Cont at 12 months among those who fail to use the Quitline after both the AAC and TM interventions? Secondary analyses will compare embedded dynamic treatment regimens.

#### Primary analyses for reach

Our primary analyses of Reach will be performed using generalized estimating equations (GEE) to account for clustering of patients within clinic [71, 72]. We will use robust standard errors used for statistical inference, which will incorporate appropriate upward covariance adjustment to correct for the downward bias of these estimates when the number of clusters is limited [73]. Separate analyses will be applied for the different treatment comparisons at each stage of the three-phase design. At each phase, GEE will be applied to a binary outcome model and will include the CHC as a clinic-level factor and patient level covariates as predictor variables to control for baseline imbalances that can occur when clinic level randomization is used [74]. The GEE analyses for the phase 2 and phase 3 treatment comparisons will also include indicator variables for the patients’ randomized assignments at previous phases as covariates.

Our primary analyses will estimate (1) the effect of the AAC-Out vs. AAC-In on Reach at 2 weeks for the full cohort of all randomized patients, (2) the effect of TM vs. CO on 6-month Reach in the subcohort without UTQL use by week 2, and (3) the effect of the TM + MAPS vs. TM on month 12 Reach in the subcohort with no UTQL use by month. Our primary phase 2 and phase 3 comparisons will average over patients exposed to different interventions in the previous phases. Secondary contrasts will compare the effects of the phase 2 and phase 3 interventions within subgroups exposed to specific interventions in the earlier phases.

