### Setting

Thirty-three primary care clinics within 11 CHC organizations will be recruited to participate in the project. All CHC organizations and clinics will be recruited in partnership with the Association for Utah Community Health (AUCH), the federally designated Primary Care Association that represents Utah’s 13 CHC organizations. The 11 participating CHCs serve ~ 88,000 unique adult patients annually with a mix of patient demographics, including > 50% minority (48% Latino; 9% American Indian), 52% uninsured, and 68% living under the federal poverty level [56]. CHCs range in size from one to seven primary care clinics per organization and include both rural and urban clinics.

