**Fig. 3 Fig3:**
[figure not shown]
Clinic and patient flow diagram

In the first phase, clinics will be randomized to either AAC-In or AAC-Out. After the initial clinical encounter with a patient, those patients who do not enroll in UTQL treatment in response to the AAC condition after ~ 2 weeks will be individually randomized to receive either text messaging (TM) or continued AAC only (CO) in a 4:1 ratio (4 to TM for every 1 to CO). Patients who enroll in the UTQL receive no further interventions. Six months after the clinical encounter, participants in the TM condition who are non-responders (i.e., have not enrolled in UTQL treatment) will be randomized to receive either continued text messages (TM-Cont) or text messages + MAPS (TM + MAPS) in a 1:1 ratio. Patients who enroll in UTQL receive no further interventions. All randomization sequences will be generated using random permuted blocks with random block sizes to assure balanced randomization over time. Clinic randomization will be stratified by CHC and clinic size, with several of the smaller CHCs grouped into the same stratum to provide sufficient clinics for stratification by clinic size within this stratum. Patient-level randomization will be stratified by clinic and by the treatment groups of earlier phases in the SMART design.

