#### Statistical power

The power calculations for the AAC-Out vs. AAC-In comparison assume an intraclass correlation for each outcome of 0.02 and a coefficient of variation of the clinic sizes of 0.88 based on a census of the 33 participating clinics. The calculations for TM vs. CO in phase 2 assume ≥ 80% of subjects fail to use the UTQL by week 2, and the calculations for TM + MAPS vs. TM-Cont in phase 3 assume both that ≥ 80% of subjects fail to use the UTQL by week 2, and ≥ 80% of those assigned to TM in phase 2 fail to use the UTQL by month 6. Under these assumptions, the 6000-patient SMART design will provide 80% power (two-sided α = 0.025 to account for two co-primary outcomes) to detect increases in Reach of 6.2%, 2.8%, and 3.6% from assumed control group percentages of 10%, 5%, and 10%, for the AAC-Out vs. AAC-In, TM vs. CO, and TM + MAPS vs. TM-Cont. comparisons, respectively. The corresponding minimum detectable effects for Impact are 3.5%, 1.5%, and 1.9%, relative to assumed control group percentages of 2.0%, 1.0%, and 2.0%, respectively.

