### Update to study design and statistical analysis

In the time from submission of this manuscript to acceptance, there has been a change in the study protocol. First, two clinics within a single CHC organization combined to form one clinic. Therefore, our total sample of clinics will change from 33 clinics to 32 clinics. Second, the study team was unable to develop an ‘Opt-Out’ version of AAC in one of the EHR systems due to technical limitations (as described in the discussion). Therefore, the Phase 1 randomization will occur only among the CHC clinics that use the two EHR systems that can be configured to both AAC-In and AAC-Out (*n* = 21 clinics). Clinics that use the third, nonconfigurable EHR will not be randomized in phase 1 (*n* = 11 clinics), and will all receive the EHR intervention of AAC-In. Patients in clinics using the nonconfigurable EHR will be randomized in the patient level randomizations (Phase 2 and Phase 3). Our primary analyses of the AAC-Out vs AAC-In comparison will be restricted to the 21 clinics with EHRs that allow them to be randomized to either condition, and will thus exclude the clinics that use the EHR that cannot be configured to AAC-Out. Comparisons of TM vs. CO and of TM+MAPS vs. TM will be performed for patients who receive care in all 32 clinics. The updated power calculations for the AAC-Out vs. AAC-In comparison continue to assume an intraclass correlation for each outcome of 0.02, and now assume a coefficient of variation of the clinic sizes of 0.96 based on a census of the 21 participating clinics that use the two configurable EHRs. The 21 clinics have a projected total of 4,019 patients out of the projected total of 6,000 patients across all 32 participating clinics. Our updated power analyses indicate that the minimum detectable effect for Reach of the AAC-Out vs. AAC-In comparison is an 8.1 percentage point increase in AAC-Out relative to an estimated reach of 10% in AAC-In. The corresponding minimum detectable effect for Impact is 4.8 percentage points in AAC-Out relative to an assumed Impact of 2.0% in AAC-In. In addition to these changes in the design and power calculations, we have also modified our plans for addressing missing abstinence data in the computation of the Impact Outcome. We now plan to apply multiple imputation in cases where patients who fail to respond to the abstinence questionnaire.

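### The Phase 1 model adjusts for each CHC although clinic randomization pooled the smaller CHCs, so any CHC with all its clinics in one arm adds essentially nothing to AAC-Out vs AAC-In

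*Protocol article*

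**What the plan says.** The primary analysis of Reach uses "generalized estimating equations (GEE) to account for clustering of patients within clinic". At each phase, "GEE will be applied to a binary outcome model and will include the CHC as a clinic-level factor", together with patient covariates. Primary analyses for impact applies the same kind of model to Impact.

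The Study design section stratifies clinic randomization by CHC and clinic size, but "with several of the smaller CHCs grouped into the same stratum to provide sufficient clinics for stratification by clinic size within this stratum". The Setting section states that "Thirty-three primary care clinics within 11 CHC organizations will be recruited to participate in the project" and that "CHCs range in size from one to seven primary care clinics per organization".

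The Update to study design and statistical analysis reduces the total to 32 clinics and narrows Phase 1: "Our primary analyses of the AAC-Out vs AAC-In comparison will be restricted to the 21 clinics" whose EHR can be set to either condition. It adds that "The 21 clinics have a projected total of 4,019 patients out of the projected total of 6,000 patients". It does not change the model. Nowhere does the article say that the pooled stratum stands in for the individual CHCs in the analysis.

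**The concern.** The analysis factor is finer than the randomization factor. Pooling balances the arms across the small CHCs taken together, not within each one. A small CHC can therefore have only one arm, and a single-clinic CHC must. With a separate level for each CHC, the arm effect is estimated from differences between clinics of the same CHC. A CHC with one arm offers no such difference.

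At stake is precision in the comparison with the fewest independent units. The article sets out to estimate the Phase 1 effect in the full randomized cohort, and its detectable effects credit all 21 clinics. If some of them carry no weight in the contrast, the precision is lower than those figures imply, unless the CHC factor earns it back by removing variation between CHCs.

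**Working it through.** **Inputs.** From the Update: 21 clinics, 4,019 patients, ICC 0.02, coefficient of variation (CV) of clinic size 0.96, and detectable effects of 8.1 points from 10% (Reach) and 4.8 points from 2.0% (Impact). From Statistical power: 80% power, two-sided α = 0.025; for the original design, 33 clinics, 6,000 patients and CV 0.88, with effects of 6.2 and 3.5 points. The number of clinics per CHC among the 21 is not given and is assumed below.

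**1. Reproducing the plan's figures.** With mean clinic size m and λ = m / (m + (1 − ICC)/ICC), the design effect is DE = [1 + (m − 1)·ICC] / [1 − CV²·λ(1 − λ)]. The detectable difference d solves d = (2.241 + 0.842)·√(DE·[p₁(1 − p₁) + p₂(1 − p₂)]/(N/2)), with p₂ = p₁ + d.

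- Original: m = 6000/33 = 181.8, λ = 0.788, DE = 4.616/0.871 = 5.30. Result: 6.15 and 3.46 points (stated 6.2 and 3.5).
- Updated: m = 4019/21 = 191.4, λ = 0.796, DE = 4.808/0.850 = 5.65. Result: 7.97 and 4.68 points (stated 8.1 and 4.8). Power at the stated effects is 81.3% and 81.6%.

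The stated figures therefore follow from a formula that has no CHC term and counts all 21 clinics.

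**2. The mechanism.** It was checked on one simulated data set with 21 clinics, an assumed 7, 5, 3, 2, 1, 1, 1, 1 clinics per CHC, and a logistic GEE clustered by clinic. All outcomes in the single-clinic AAC-Out CHCs were replaced by a 50% rate.

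- CHC as factor: estimate and standard error unchanged (log odds ratio −0.0144, SE 0.2524). With a patient covariate the estimate moved only from −0.013 to −0.004, hence *essentially* nothing.
- Pooled stratum as factor: the estimate moved from 0.05 to 0.66.

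**3. How many clinics, and how much information.** With equal clinic weights, a group with n₁ and n₀ clinics per arm carries information n₁n₀/(n₁ + n₀). CHCs with one or two clinics are assumed to form the pooled stratum. For 7, 5, 3, 2, 1, 1, 1, 1:

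- Randomization grouping: 12/7 + 6/5 + 2/3 + 9/6 = 5.08.
- CHC factor: 12/7 + 6/5 + 2/3 + (3/5)(1/2) = 3.88. The two clinics of the two-clinic CHC share an arm with probability 2/5.
- Clinics lost on average: 4 + 2(2/5) = 4.8. Ratio 3.88/5.08 = 0.764, so the variance is 1/0.764 = 1.31 times as large.

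| Assumed clinics per CHC | Mean clinics lost | Information kept | Variance ratio |
|---|---|---|---|
| 7, 5, 4, 3, 1, 1 | 2.0 | 0.902 | 1.11 |
| 6, 4, 3, 3, 2, 2, 1 | 2.6 | 0.881 | 1.14 |
| 7, 5, 3, 2, 1, 1, 1, 1 | 4.8 | 0.764 | 1.31 |
| 7, 6, 4, 4 | 0 | 1 | 1.00 |

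If each CHC uses one EHR, all of these fit 11 CHCs, 32 clinics and at most seven clinics per CHC. A ten-CHC layout does not: it would leave 32 − 21 = 11 clinics to a single CHC.

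**4. Unequal clinic sizes and the split of the ICC.** Weighting clinics by size (CV 0.96) and simulating the stratified randomization over compatible layouts with small CHCs gives these variance ratios, CHC factor against randomization grouping:

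| Share of ICC between CHCs | Variance ratio |
|---|---|
| none | about 1.10-1.33 |
| half | about 1.05-1.15 |
| three quarters | about 0.95-1.00 |

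**5. Effect on the stated figures if all of the ICC is at clinic level**, reusing the formula in step 1 with the lost clinics removed (same mean size and CV):

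| Clinics lost | Reach, points | Impact, points | Power at 8.1 points |
|---|---|---|---|
| 0 | 7.97 | 4.68 | 81% |
| 2 | 8.43 | 5.00 | 77% |
| 3 | 8.69 | 5.19 | 74% |
| 4 | 8.97 | 5.39 | 72% |
| 5 | 9.29 | 5.62 | 69% |

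**The case against.** Adjusting for CHC is a legitimate choice. It causes no bias, and it removes variation between CHCs, which the power formula does not credit. That offset is real. With half of the ICC between CHCs, power at 8.1 points with the CHC factor is about 91% for a 7, 7, 5, 1, 1 layout and 87% for 7, 5, 3, 2, 2, 1, 1, with detectable effects of 6.9 and 7.3 points. With three quarters between CHCs, the penalty disappears or slightly reverses. The documents give no split.

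The range of one to seven clinics describes the 11 CHCs before the Update. Nothing shows that a single-clinic CHC remains among the 21. A full analysis plan might also define the factor as the grouped stratum. This makes the size conditional, but the article states both the model and the stratification, and the two differ.

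A reader might infer more than the documents support:

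- *Phase 1 is underpowered, or its stated effects are wrong.* The figures reproduce under their own assumptions, and a shortfall appears only if clinics are lost and little of the ICC lies between CHCs.
- *The small-sample standard error breaks down for a clinic alone in its CHC.* The article does not name the correction, and not every correction has this problem.
- *Phases 2 and 3 lose clinics too.* Patients there are randomized within clinic, so a single-clinic CHC contributes fully.

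**Conclusion.** The mismatch stands for Phase 1. Any CHC among the 21 clinics without both arms adds essentially nothing to AAC-Out vs AAC-In under the stated model, while the detectable effects count every clinic. For the layouts tried, about 2 to 5 clinics are lost. The variance penalty is about 10-33% with all of the ICC at clinic level, about 5-15% with half between CHCs, and none when most lies between CHCs. It is zero if every CHC has both arms. These layouts illustrate a range and do not bound it. They assume that CHCs with one or two clinics were pooled and that each CHC uses one EHR. The issue is precision, not bias.

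**What to change.** In the Phase 1 GEE for Reach and Impact, replace the CHC factor by the CHC grouping used in the clinic randomization: one level for each CHC that formed its own stratum and one shared level for the pooled small CHCs. Leave the Phase 2 and Phase 3 models as they are.

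This takes one sentence in the analysis plan, written before outcomes are compared by arm, and needs no new data. Its downside is that differences between the pooled CHCs remain in the error term, which matters more as the between-CHC share of the ICC grows.

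If the CHC factor is kept, state how many of the 21 clinics contribute to the contrast and restate the Reach and Impact detectable effects on that basis. The sponsor can count them directly from the clinic list and allocation.

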#### Primary analyses for impact

GEE analyses with a binary outcome model will also be used for Impact, defined by a binary indicator which is equal to 1 only for patients who both use the UTQL by a designated follow-up time and are abstinent at month 12. We will also evaluate efficacy by conducting secondary analyses to compare 12 month abstinence among patients assigned to the respective treatments (or treatment regimens) within the subgroups who use the UTQL by the designated follow-up times. For example, the effect of AAC-Out vs. AAC-In on efficacy will be evaluated by comparing the proportions of patients who report 12 month abstinence between those in the AAC-Out and AAC-In groups who use the UTQL by 2 weeks.

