#### MAPS

Patients will receive brief counseling calls by health coaches trained in Motivation And Problem Solving (MAPS) [44–46]. MAPS is designed to help patients address the larger context in which tobacco use occurs, motivate patients towards a long-term goal of quitting tobacco, and identify and address barriers to quitting and engaging in treatment. MAPS has demonstrated effectiveness for addressing the entire cessation process of considering quitting, cessation, and Quitline treatment engagement [30–32, 60].

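### A quit-rate comparison among Quitline users only is called the effect of the arm on efficacy, although Quitline use is itself an outcome of the arm

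*Protocol article*

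**What the plan says.** *Primary analyses for impact* announces the efficacy analyses as secondary: "We will also evaluate efficacy by conducting secondary analyses to compare 12 month abstinence". They compare the assigned treatments or regimens "within the subgroups who use the UTQL by the designated follow-up times". The worked example for phase 1 states that "the effect of AAC-Out vs. AAC-In on efficacy will be evaluated by comparing the proportions of patients who report 12 month abstinence", with both arms limited to patients who used the Quitline by 2 weeks.

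The same Quitline use is the first primary outcome. *Primary analyses for reach* sets out to estimate "the effect of the AAC-Out vs. AAC-In on Reach at 2 weeks for the full cohort of all randomized patients".

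Impact, the other co-primary outcome, is "defined by a binary indicator which is equal to 1 only for patients who both use the UTQL by a designated follow-up time" and are also abstinent at month 12. It is not restricted to users: a non-user stays in the denominator and scores 0.

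On data collection, the *Patient* subsection of *Outcomes measures and data collection* says: "Tobacco-using patients will be contacted to complete a self-report abstinence survey at 12 months following the initial clinical encounter". That is not limited to enrollees. Other secondary work is described in *Analytic plan* as "Secondary analyses will compare embedded dynamic treatment regimens", with no outcome named there.

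**The concern.** Every intervention in this trial is designed to change who enrolls in the Quitline. Restricting the abstinence comparison to enrollees therefore conditions on an event that occurs after randomization and that the arm is expected to shift. The users in the arm with higher Reach are a mix of patients who would have enrolled anyway and patients drawn in by the strategy. Unless both kinds quit at the same rate, the proportions differ even when the arm alters nobody's quitting. The comparison describes the composition of the user groups as much as any treatment effect, yet the text calls it an effect without qualification. The problem recurs in phases 2 and 3 and in the regimen comparisons, because the same restriction is applied there.

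A strategy that raises Reach and helps some patients could be reported as lowering efficacy, or one with no effect on quitting could be reported as raising it.

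Impact does not answer the same question. It measures quitting together with Quitline use, so a quit without enrollment counts as 0. This matters most in phase 3, where the article says that "MAPS has demonstrated effectiveness for addressing the entire cessation process of considering quitting, cessation, and Quitline treatment engagement": a patient who quits after MAPS calls without enrolling scores as a failure.

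**Working it through.** **Inputs from *Update to study design and statistical analysis*.** Phase 1 now has 21 clinics and 4,019 patients, ICC 0.02 and coefficient of variation of clinic size 0.96. AAC-In Reach is 10%, with a minimum detectable increase of 8.1 points. AAC-In Impact is 2.0%, with a minimum detectable increase of 4.8 points. *Statistical power* gives 80% power and two-sided alpha 0.025.

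**Reproducing the plan's figures.**
- Mean clinic size m = 4,019/21 = 191.4.
- L = m × ICC / (m × ICC + 1 - ICC) = 3.828/4.808 = 0.796.
- Design effect = [1 + (m - 1) × ICC] / [1 - CV² × L × (1 - L)] = 4.808/0.850 = 5.65.
- Effective size is about 355 per arm.
- A two-proportion calculation then gives power 0.81 for both outcomes at the stated effects, and minimum detectable effects of 8.0 points (Reach) and 4.7 points (Impact).

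The stated 8.1 and 4.8 are reproduced to within 0.1 point. They are not in dispute and only supply the rates used below.

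**Rates for the illustration.**
- AAC-In efficacy is Impact/Reach = 2.0/10 = 20%.
- AAC-Out Reach is 10% + 8.1% = 18.1%. This is the control rate plus a detectable effect, not a forecast.

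**Assumptions (not in the article).**
- Everyone who would enroll under AAC-In would also enroll under AAC-Out.
- AAC-Out adds 8.1% of patients, who quit at rate b with or without the Quitline.
- The arm therefore changes nobody's quitting, and the true difference in abstinence among all patients is 0.
- The article gives no value for b, so a range of 5% to 30% is shown.

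**Formulas.**
- Efficacy among AAC-Out users = (0.10 × 0.20 + 0.081 × b)/0.181.
- Contrast with AAC-In = 0.081 × (b - 0.20)/0.181, which is zero only at b = 0.20.
- Impact difference = 0.081 × b.

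| b | Efficacy AAC-In | Efficacy AAC-Out | Apparent effect (points) | Impact difference (points) | True difference in quitting (points) |
|---|---|---|---|---|---|
| 5% | 20.0% | 13.3% | -6.7 | +0.4 | 0 |
| 10% | 20.0% | 15.5% | -4.5 | +0.8 | 0 |
| 15% | 20.0% | 17.8% | -2.2 | +1.2 | 0 |
| 20% | 20.0% | 20.0% | 0.0 | +1.6 | 0 |
| 30% | 20.0% | 24.5% | +4.5 | +2.4 | 0 |

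With the 6.2-point increase stated for the 33-clinic design (Reach 16.2%), the same range of b gives -5.7 to +3.8 points, so the result does not hinge on 18.1%.

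**A case with real benefit.** Suppose the added users quit at 10% with the Quitline and 5% without it. The true gain among all patients is 0.081 × 0.05 = +0.4 points, Impact shows 0.081 × 0.10 = +0.8 points, and the user-only contrast shows -4.5 points.

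**The case against.** The strongest reply is that little rests on this contrast. It is labelled secondary, and *Multiple comparisons* treats everything beyond the Reach and Impact hypotheses as secondary or exploratory. Efficacy is by definition the second factor of Impact, so it would be read beside Reach and Impact. In the b = 10% row a reader would see Reach up 8.1 points and Impact up 0.8 points next to the lower efficacy, and could work out why. This limits the harm and stands. It does not make the contrast a randomized effect.

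The reply also guards against four stronger readings that a reader might infer:

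- **That Impact is biased or invalid.** It is not. It keeps every patient in the randomized comparison. Counting only quits that accompany Quitline use is a choice of estimand, and it fits a trial whose stated aims are Reach and the Impact of Quitline treatment.
- **That the trial plans no analysis of quitting overall.** This can be said only of the article. The statistical analysis plan is not shown and may contain one.
- **That the bias makes a successful strategy look worse, because added users are less motivated.** The article says nothing about their motivation or quit rate. The direction is unknown.
- **That Impact overstates the true gain by a fixed factor, such as two.** Any such factor follows from an assumed quit rate without the Quitline, which the article does not give.

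**Conclusion.** The concern holds for the label and for the choice of secondary comparison. Abstinence among Quitline users by arm is not an effect of the arm on efficacy, because membership of the user group is an outcome of the arm. At the plan's own rates the resulting artefact could be several points in either direction against a baseline efficacy of 20%. Its exact size depends on the added users' quit rate, on nobody being deterred from enrolling by AAC-Out, and on Reach rising by the detectable amount; none of these is known. The primary tests are unaffected. What is missing from the article's description is a comparison of abstinence by randomized arm that does not depend on Quitline use, although its stated objective is lower tobacco use prevalence.

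**What to change.** In *Primary analyses for impact*:

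1. Report quit proportions among users by arm as descriptive components of Impact, and remove the wording that presents their difference as an effect of the arm.
2. Make the secondary abstinence comparison 12-month abstinence among all patients in each randomized comparison, whatever their Quitline use. The sets are the 21 randomized clinics for phase 1 and the re-randomized non-responders for phases 2 and 3. Use the same GEE model, and extend multiple imputation to non-users.

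The survey is already described as going to tobacco-using patients generally, so no new instrument is needed. There are three costs:

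- **Missing data.** Impact is 0 for non-users whatever their abstinence, so it needs survey answers only from users, and the planned imputation is tied to Impact. The all-patient comparison needs answers, or imputed values, from the majority who do not enroll.
- **Power.** If abstinence in the control arm were 10% (an assumption), the effective sample of about 355 per arm in phase 1 detects about 8 points, against a true gain of 0.4 points in the example with benefit. The result should be read as an estimate with a confidence interval.
- **Interpretation.** At 12 months the phase 1 and phase 2 comparisons include whatever later assignments followed, and should be described that way.
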